### Statistical analyses

All scales used in the analysis will be validated using confirmatory factor analysis and reliability analyses. The intervention and wait-list control group will then be compared in terms of baseline measures for symptoms, health behaviour and wellbeing as well as possible confounds such as accessibility/remoteness and gender. Two multi-level modelling analyses will then be conducted. In the first analysis, the intervention and control group will be compared in relation to pre, post and follow-up changes for symptoms, health behaviour and wellbeing. In this analysis, significance levels will be adjusted to reflect the multiple primary outcome measures. In the second multi-level analysis only the intervention group will be considered, with fortnightly changes in the K10 compared in terms of the specific symptom-based programs that were completed by each participant during the previous fortnight (or previously in their intervention).

### Sample size and power calculations

GPower [60] analysis indicates that to detect a small to medium effect size (*f* (V) test = .15) with power of at least .80 and an alpha level of .05, a sample size of 38 participants per condition is sufficient, assuming that all these participants complete all questionnaires. Because drop-out rates at follow-up stage have been reported as high as 70% [61] in trials of Internet-based mental health interventions, it is proposed that a total of 200 young people be recruited initially.

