### Primary outcomes

The primary outcomes being assessed are reduction in anxiety and/or depressive symptoms. Validated questionnaires will be used to measure generalised anxiety (Generalised Anxiety Disorder 7 [46]), panic (Panic Disorder Severity Scale [47]), obsessions and compulsions (Obsessive-Compulsive Inventory-Revised [48]), social anxiety (Social Phobia Inventory [49]), posttraumatic stress (Posttraumatic Stress Disorder Checklist-Civilian Version [50]), specific fear (the Fear Questionnaire [51]) and depressive symptoms (Patient Health Questionnaire-9 [52]). These measures are also being used to determine whether participants are eligible to receive specific symptom content in their tailored online program.

In addition, an online screening device (eScreener) was developed in 2011 to measure anxiety and depressive symptoms. This eScreener will be compared against the validated questionnaires in order to develop a shorter means of determining symptom content for the online program. Once the eScreener is validated future entry to the program will first involve an assessment of psychological distress (with the Kessler-10 scale; K10 [53, 54]), with alternate referral recommendations with people with little or very high distress, and then administration of the eScreener as the sole means of determining symptom relevant content.

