### Hypotheses

It is hypothesised that at the post-intervention (week 8) and follow-up (week 20) assessment stages, participants assigned to access the intervention immediately will have fewer anxiety and depressive symptoms than those assigned to the wait-list control group.

In addition, it is hypothesised that at post-intervention and follow-up participants allocated to the intervention group will have less psychological distress, reduced internalised homophobia, greater life satisfaction, wellbeing, greater perception of control over their health, and more positive help-seeking attitudes than participants in the wait-list control group.

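### The sample size is powered at an unadjusted alpha of .05, but the primary between-group analysis will use levels adjusted for several primary scales, so the stated power is not that of the planned test

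*Protocol article*

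**What the plan says.** Under Sample size and power calculations, the protocol article sets out "to detect a small to medium effect size (*f* (V) test = .15", "with power of at least .80 and an alpha level of .05", and concludes that "a sample size of 38 participants per condition is sufficient, assuming that all these participants complete all questionnaires". It then notes that "drop-out rates at follow-up stage have been reported as high as 70" per cent in comparable trials, and for that reason "it is proposed that a total of 200 young people be recruited initially".

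Under Primary outcomes: "The primary outcomes being assessed are reduction in anxiety and/or depressive symptoms". That section and Table 1 list seven instruments as primary: depressive symptoms, generalised anxiety, panic, social anxiety, obsessions and compulsions, posttraumatic stress and specific fear. None is singled out as the lead, and no composite is defined.

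Under Statistical analyses, the first multi-level analysis compares the two groups on change across the pre, post and follow-up assessments. For that analysis, "significance levels will be adjusted to reflect the multiple primary outcome measures".

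Under Hypotheses, the symptom benefit is expected "at the post-intervention (week 8) and follow-up (week 20) assessment stages".

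**The concern.** The two sections describe different tests. One sizes the trial for a single test at .05. The other commits the between-group analysis to levels adjusted across the primary measures. Any family-wise adjustment over seven unranked scales begins below .05, so the power of .80 cannot be carried over to a given scale.

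This conflict stands in the text and is not a missing detail. An analysis plan could name the adjustment method, but it could not turn a calculation made at .05 into one made at a lower level.

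What is at stake is how a null result is read. A reader who relies on .80 would take a non-significant scale as fair evidence of no useful effect. At the number of completers that the protocol calls sufficient, the chance of detecting the planned effect on that scale may be little better than even.

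**Working it through.** **Inputs from the protocol article:** effect size .15; alpha .05; target power .80; 38 per condition (76 in total); 200 recruits; drop-out up to 70%; two equal groups; three measurements (weeks 0, 8, 20); seven primary scales.

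**Assumed, because not stated:** correlation between repeated measurements ρ = .5; sphericity; Bonferroni as the adjustment.

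**Model.** Repeated-measures group-by-time F test with k = 2 groups and m = 3 measurements:

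- noncentrality λ = f² · N · m / (1 − ρ)
- df1 = (k − 1)(m − 1) = 2
- df2 = (N − k)(m − 1) = 2(N − 2)
- power = P(noncentral F > critical F at the chosen alpha)

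**Step 1: reproduce the stated figure.** At N = 76, λ = .0225 × 76 × 3 / .5 = 10.26 and df2 = 148. At alpha .05 power is .818. The smallest even N reaching .80 is 74 (37 per condition), so 38 per condition is reproduced closely.

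**Step 2: change only alpha.** .05 / 7 = .00714.

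| Completers | Drop-out from 200 | λ | Power at .05 | Power at .05/7 |
|---|---|---|---|---|
| 60 | 70% | 8.10 | .71 | .43 |
| 76 | 62% | 10.26 | .82 | .57 |
| 100 | 50% | 13.50 | .91 | .74 |
| 112 | 44% | 15.12 | .94 | .80 |
| 140 | 30% | 18.90 | .98 | .90 |
| 200 | 0% | 27.00 | .998 | .98 |

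The first even N with power of at least .80 at .05/7 is 112, or 56 per condition. As a share of recruits, 112 / 200 = .56, so drop-out may be at most 44%. If drop-out were 70%, 112 / .30 = 373.3, so 374 would have to be recruited.

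**Step 3: sensitivity to the adjustment, at 76 completers.** Šidák over seven gives .57. Dividing alpha by only two gives .73 and by three gives .68. Under Holm, a scale faces .567 at the first step, and then .587, .612, .641, .680, .733 and .818. It reaches the last value only when the other six scales have already been rejected.

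**Step 4: sensitivity to the model.**

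- If the intended input was f²(V) = .15 in a repeated-measures MANOVA with three measurements, power at 76 falls from .85 to .61.
- If f(V) = .15 is taken literally, power at 76 is only .19 at .05 and falls to .05. That reading does not give 38 per condition.
- A generic one-degree-of-freedom test designed for exactly .80 at .05 falls to .54 at .05/7.

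The direction holds on every reading. On those that come near the stated sample size, the loss is about a quarter in absolute power.

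**The case against.** **The trial recruits 200, not 76.** It is tempting to say that power on each scale is far below .80 without qualification. The protocol does not support that. The 70% is the upper end of what has been reported, not a forecast. With 112 or more completers the adjusted test still reaches .80, and with 140 it reaches .90. This stands, so the size of the shortfall must always be tied to a number of completers. It does not rescue the statement that 38 per condition is sufficient, and 70% is the rate that the protocol itself uses to justify 200.

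**Completer-based power is pessimistic.** The planned multi-level model can use partial data, and later Holm steps are less strict. Both points stand and soften the figures somewhat.

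**The model is inferred.** The correlation, sphericity and Bonferroni are assumptions, and the f(V) label taken literally does not reproduce the sample size. The two-digit values are therefore approximate. The mismatch in alpha does not depend on them.

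**Two assessment times.** A reader might infer from the hypothesis about weeks 8 and 20 that there are 14 primary tests, that power should be judged at .05/14, and that adjusting for scales alone leaves the family-wise error above .05. The documents do not establish this. The analysis section describes one comparison of change over all three assessments, which can be a single test per scale and hence seven tests. Applying .05/14 to that joint test would also give the power of no planned contrast. The point arises only if the weeks are tested separately.

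**No arithmetic slip.** The 38 per condition is consistent with its own alpha. The fault is that this alpha is not the one the primary analysis will use.

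**Conclusion.** The point holds as an inconsistency between the sample size section and the statistical analyses section: the stated power of at least .80 is not that of the planned adjusted test.

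If Bonferroni over seven is used, and on the repeated-measures reading that reproduces the stated sample size, power per scale is about .57 instead of .82 at 76 completers. At 60 completers it is about .43 instead of .71. Whether the trial as recruited falls short depends on drop-out, with the dividing line at about 44%. The documents support neither an unconditional claim of low power nor a claim that error across the scales is uncontrolled, since an adjustment for the scales is already promised.

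**What to change.** In Sample size and power calculations, restate the power and the required number of completers at the adjusted significance level. Name:

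- the adjustment method;
- the number of tests it covers;
- the statistical model, with the correlation and sphericity assumed;
- the highest drop-out rate at which 200 recruits still give .80 (44% under the assumptions used here).

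If week 8 and week 20 are to be tested separately on each scale, say so in Statistical analyses, count both in the adjustment, and compute power for those contrasts and not for the joint test.

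Settle this before outcome data are analysed, so that the adjustment cannot be chosen in the light of the results. It requires no extra data and no change of endpoint. The cost is a less favourable power statement.

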**Methods/Design:**

We are recruiting, through media and community organisations, 200 same-sex attracted young adults with anxiety and/or depressive symptoms and mild to moderate psychological distress (Kessler-10 score between 16 to 21). Participants will be randomly allocated to the intervention (the online program) or the wait-list control group based on a permuted blocked randomisation method to allow for stratification by gender. Participants in the intervention group will receive a tailored program for up to three types of mental health difficulties simultaneously. The primary outcome of anxiety and/or depressive symptoms, and secondary outcomes related to psychological distress, wellbeing and health behaviour will be measured at pre-intervention (0 week), post-intervention (8 weeks) and at a 3-month follow-up (20 weeks).

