### Randomisation

An automated computerised randomisation system will generate random sequences for group allocation. This will be based on a permuted blocked (block size = 10) randomisation method to allow for stratification by gender, ensuring that equal gender numbers are allocated to each of the two conditions. Trial enrolment, randomisation and assignment to intervention will all be automated and will not require any human input.

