Secondly, participant drop-out is a potential challenge, particularly given the self-help nature of the intervention [64]. To enhance motivation, the program modules are deliberately brief and incorporate interactive exercises, videos, audios, pictures and downloadable tip sheets. Contact details are provided on the website in case of questions or technical details. To encourage survey completion automated Emails are sent to participants and they are required to complete the K10 every 2 weeks while in the program in order to regain access to content. Sample size and power calculations have taken into account potential attrition and a conservative intention-to-treat analysis will be complimented with a longitudinal multi-level analysis to ameliorate the effects of drop-out at follow-up.

A third potential limitation is that the intervention is being compared to a wait-list control group, whereby participants will be able to access alternate evidence-based mental health services, including CBT. Information will be collected from participants about mental health service usage and the potential impact of this on outcomes will be statically controlled for.

In summary, SSAYA are at greater risk of poor mental health outcomes compared to their heterosexual peers. The provision of a preventive online mental health and wellbeing program, tailored to the gender and symptoms of the participant, may provide a cost-effective, anonymous and flexible medium for improving mental health outcomes for these individuals.

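### At the highest drop-out rate the protocol cites (70%), 200 recruits leave 30 completers per condition, short of the 38 its power statement requires; 200 suffices only up to 62% drop-out

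*Protocol article*

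**What the plan says.** The protocol article, under Sample size and power calculations, sets the target "to detect a small to medium effect size (*f* (V) test = .15") with "power of at least .80 and an alpha level of .05". It concludes that "a sample size of 38 participants per condition is sufficient, assuming that all these participants complete all questionnaires". The next sentence gives the reason for a larger intake: "drop-out rates at follow-up stage have been reported as high as 70" per cent in trials of internet-based mental health interventions, and so "it is proposed that a total of 200 young people be recruited initially".

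The Randomisation section describes blocked allocation stratified by gender, "ensuring that equal gender numbers are allocated to each of the two conditions". I read this as 1:1, or 100 per condition.

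The Discussion, on its second limitation (participant drop-out), says: "Sample size and power calculations have taken into account potential attrition". It adds that a longitudinal multi-level analysis is meant to soften the effect of losses at follow-up.

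**The concern.** The power statement is conditional on 38 full completers in each condition. The intake of 200 is presented as the answer to drop-out, and 70% is the only rate named. A reader will therefore assume that 200 recruits preserve the 38 at that rate. They do not, and the drop-out that 200 can absorb is not stated anywhere.

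The hypotheses include a comparison at week 20, which is the stage the 70% refers to. If losses there approach the cited rate, a null result would be read against a power of at least .80 whose stated condition was not met.

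**Working it through.** **Inputs from the protocol article**
- Completers required: 38 per condition, 76 in total (Sample size and power calculations)
- Highest cited drop-out at follow-up: 70% (same section)
- Recruits: 200 (same section); equal allocation, so 100 per condition (Randomisation)
- Effect .15, alpha .05, power at least .80 (Sample size and power calculations)
- Assessments: 3, at weeks 0, 8 and 20 (Abstract and Study design)

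**Step 1. Can the stated 38 be reproduced?** The article does not name the test, the correlation between assessments or a sphericity correction, so these are my assumptions. I used a repeated-measures F test of the group-by-time interaction with k = 2 groups, m = 3 assessments, ordinary f = .15, correlation rho = .5 and sphericity:

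lambda = f² × N × m / (1 − rho), df1 = (k − 1)(m − 1) = 2, df2 = (N − k)(m − 1).

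- N = 74: power .806, the smallest even N that reaches .80 (37 per condition)
- N = 76: lambda = 0.0225 × 76 × 3 / 0.5 = 10.26, df2 = 148, power .818

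This comes within one participant per condition of the stated 38, so it is a plausible reconstruction but not a confirmed one.

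**Step 2. Completers left at 70% drop-out.** 200 × (1 − 0.70) = 60, or 30 per condition. Shortfall: 38 − 30 = 8, and 8/38 = 21%.

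**Step 3. Recruits needed to keep 38 at 70%.** 38 / 0.30 = 126.7, rounded up to 127 per condition, 254 in total.

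**Step 4. Largest drop-out that 200 can absorb.** 1 − 76/200 = 0.62, or 62%.

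Steps 2 to 4 use no assumption beyond equal groups and equal loss in each.

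**Step 5. Illustrative effect on power.** In the setting of step 1, N = 60 gives lambda = 0.0225 × 60 × 3 / 0.5 = 8.10, df2 = 116, power .711. Varying the unstated correlation:

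| Assumed correlation | Power at 60 completers | Power at 76 completers | Difference |
|---|---|---|---|
| .3 | .556 | .667 | .111 |
| .4 | .626 | .739 | .113 |
| .5 | .711 | .818 | .107 |
| .6 | .810 | .898 | .088 |
| .7 | .911 | .964 | .053 |

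Of these correlations, .5 comes closest to a requirement of 38 per condition. At .3 the requirement would be 102 in total, and at .7 it would be 46.

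Other readings of the effect size give other levels:
- A two-group multivariate test with three responses and f² = .15 needs 77 in total, and gives .796 at 76 and .677 at 60.
- Taking the article's f(V) notation literally, with lambda = f² × (N − k)(m − 1), the requirement is 218 in total, and power is about .35 at 76 and .28 at 60.

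**The case against.** **The 70% is a ceiling, not a planning rate.** The article says rates have been reported as high as this. It does not say that 70% is expected, or that 200 was obtained by dividing 76 by 0.30. An intake of 200 is 2.6 times the 76 required, a substantial allowance. This stands, and it rules out saying that the trial will be underpowered. It does not remove the mismatch: 70% is the only rate given and the stated reason for 200, and no lower planning rate appears.

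**The Discussion's sentence is not false.** It claims only that attrition was taken into account, and raising the intake from 76 to 200 does that. A reader might infer cover at 70%, but the sentence does not promise it. It needs a limit added, not a retraction.

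**The planned model can use partial data.** The main analysis is multi-level over pre, post and follow-up, so a participant who answers at week 8 but not at week 20 still contributes. The hypotheses also cover week 8. Thirty per condition is a complete-case count at the last assessment, and .71 is not the power of the planned model. That stands too. However, the article's own .80 is conditioned on complete questionnaires, and it gives no power for the partial-data case.

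**A stronger reading to avoid.** A reader might infer that attrition takes power from .82 down to .63 or .56. Those lower values belong to correlations of .4 and .3, at which 76 completers would already give only .74 and .67. At correlations of .6 or .7, 60 completers would exceed .80, although those settings do not lead to a requirement of 38. The document gives no correlation, so none of these can be presented as the trial's power.

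**Conclusion.** The point holds as an arithmetic mismatch within one section. At the highest drop-out the protocol cites, its intake yields 30 completers per condition against the 38 it says it needs, a shortfall of 21%. The stated complete-case condition for power of at least .80 is met only if drop-out is at most 62%. This rests on the printed figures and equal groups.

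The loss of power is less certain. About .71 against .82 is a fair illustration under f = .15, three assessments, correlation .5, sphericity, unadjusted alpha .05 and complete cases only. It should not enter the protocol as fact. The unadjusted alpha is a real caveat, because the Statistical analyses section says significance levels will be adjusted for multiple primary outcomes. If that meant dividing alpha by the seven primary measures (my assumption), the same setting would give about .57 at 76 completers and .43 at 60.

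**What to change.** Restate the last part of the sample size section along these lines: recruiting 200 yields the required 38 completers per condition provided drop-out is no more than 62%; at the highest rate cited, 70%, 30 per condition would remain, and the complete-case condition for power of at least .80 would not be met.

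In the Discussion, qualify the remark on attrition to say that the calculation allows for drop-out up to 62%.

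If a power figure for 30 per condition is given, label it illustrative and list its assumptions: effect size, number of assessments, correlation, sphericity, unadjusted alpha and complete cases only. If a planning rate below 70% was intended, state it.

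The cost is a few sentences of wording and a less favourable statement of what 200 recruits secure. The correction requires no change to recruitment, design or analysis.

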### Ethical approval and trial registration

The proposed study will be conducted in accordance with the ethical guidelines outlined in the National Statement on Ethical Conduct in Human Research [62]. Ethical approval for this study was granted by the Human Research Ethics Committees of Swinburne University of Technology (SUHREC Project 2011/109) and Federation University Australia (B11-077) in June 2011. The trial has been registered with the Australian New Zealand Clinical Trial Registry since 7 July 2011: ACTRN12611000700932.

## Discussion

This paper describes the study protocol for the development and evaluation of a mental health prevention program for SSAYA. Despite having a higher incidence of mental health problems than adults 25 years of age or over [39], only 1 in 4 young people with mental health problems receive professional help and there is a shortage of trained health professionals available to help them [63]. If successful, this online intervention will represent a significant step forward in terms of prevention and early intervention of mental health problems in SSAYA, and addressing barriers associated with stigma and geographic, social and financial isolation. The anticipated strengths and potential limitations of this study are detailed below.

The proposed program is unique and sophisticated, not only in targeting the mental health needs of SSAYA but in tailoring the program content to gender and symptom profile. The personalisation of this program and online nature may help to make it more attractive and engaging for young people than traditional face-to-face alternatives. Moreover, the integrated nature of the intervention enables the simultaneous treatment of multiple mental health symptoms within one program. This is a unique feature of the program, streamlining health care for the young person, as well as acknowledging the uniqueness of each user. This is expected to be a particularly important outcome for SSAYA in rural or regional areas. We expect the findings will enhance our understanding of the impact of internalised homophobia on recovery-related outcomes. We also anticipate that the use of the control condition will enable greater insight into the unique contribution of this program compared to standard mental health and wellbeing services available to SSAYA.

Despite these strengths, three potential limitations of this study design should be acknowledged. Firstly, each participant with a different set of symptoms identified at pre-intervention assessment will get different intervention content due to their receiving content for a different number and combination of types of symptoms when they do the *Out & Online* program. The main comparison with the wait-list control group cannot take these different interventions into account but follow-up statistical analyses will target the efficacy of interventions for each symptom type in isolation and in combination with other symptom types using regression analyses.

Secondly, participant drop-out is a potential challenge, particularly given the self-help nature of the intervention [64]. To enhance motivation, the program modules are deliberately brief and incorporate interactive exercises, videos, audios, pictures and downloadable tip sheets. Contact details are provided on the website in case of questions or technical details. To encourage survey completion automated Emails are sent to participants and they are required to complete the K10 every 2 weeks while in the program in order to regain access to content. Sample size and power calculations have taken into account potential attrition and a conservative intention-to-treat analysis will be complimented with a longitudinal multi-level analysis to ameliorate the effects of drop-out at follow-up.

A third potential limitation is that the intervention is being compared to a wait-list control group, whereby participants will be able to access alternate evidence-based mental health services, including CBT. Information will be collected from participants about mental health service usage and the potential impact of this on outcomes will be statically controlled for.

In summary, SSAYA are at greater risk of poor mental health outcomes compared to their heterosexual peers. The provision of a preventive online mental health and wellbeing program, tailored to the gender and symptoms of the participant, may provide a cost-effective, anonymous and flexible medium for improving mental health outcomes for these individuals.

